**Utilization of confirmatory testing (intervention group)**

In the intervention group, participants will be provided with referral vouchers (with a unique participant ID code) that they and their partners can use for confirmatory testing (at any of the three study facilities or another facility of their choice within and around Kisumu). We will record whether participants’ partners presented these vouchers in the 3 months after enrollment in order to obtain information on utilization of confirmatory testing.

**Qualitative interviews**

We will conduct a qualitative sub-study in which we will explore in-depth the process of making a decision to suggest use of the self-test with a sexual partner; the reactions of sexual partners; the experience of using the test with a sexual partner; and decisions made after using the self-test, including sexual behavior decisions, any violence, uptake of confirmatory testing, and linkage to care.

We will conduct in-depth interviews with 45 participants from the intervention group. We will purposively sample to include 15 participants who report using self-tests as a couple, 15 who report their partner using self-tests independently, and 15 who chose not to use self-tests. We will also seek to include women who attended antenatal care and postpartum care, as well as both HIV-positive and –negative women to achieve maximum variation among qualitative participants.After the 3-month follow-up interview, the study coordinator will identify participants for the qualitative interviews in the above three categories. The study coordinator will then contact the selected participant to set up interviews. Interviews should be scheduled to take place within 1 – 2 weeks of scheduling. The interview will take approximately one hour and will be conducted at the participant’s home, the IRDO office, or another location convenient to both the participant and RA.

The qualitative data will be used to better understand women’s ability to encourage partner testing with the self-tests and gain insights on reasons why it was and was not possible for them to suggest self-test usage to their partners. The qualitative data will also enable to use to gain insights from study participants on the way their male partners reacted to the use of self-testing and explore social harms. All these elements will be important for interpreting results from the quantitative study.

## Study withdrawal for participants

Participants will be free to withdraw from the study at any time. Reasons for study withdrawal may be ascertained.

## Adverse events

Because participants will above all be making voluntary decisions to introduce self-testing with their sexual partners, we do not expect to have significant adverse events related to the usage of the self-test with partners.However, we are concerned about the safety of study participants and have prepared for the unlikely event of violence as a result of introducing the self-test to a sexual partner. During initial enrollment and counseling, we will include referral information regarding services for those experiencing IPVand we will also advise participants to use their best judgment of whether they feel comfortable introducing self-testing with a sexual partner. We are excluding from the study women who express concern that they would experience IPV as a result of suggesting HIV self-test use.Because it is possible that the sexual partners of a participant will react adversely to an HIV-positive test result, we will provide detailed oral and written information to participants on locations where IPV services, confirmatory testing, and HIV care and treatment are available. We will also set up a phone hotline for the study which will be available 24 hours per day. This hotline will be operated by the study staff, who will be available to answer questions related to the study, the use of self-test, as well as locations where participants or their sexual partners can be referred to for IPVservices, for confirmatory testing, and for HIV care and treatment. The telephone hotline will be established for use by the participants free of charge to them. Participants will be asked to “flash” the hotline number, i.e. dial the hotline and disconnect after a single ring thereby alerting the holder of the hotline that the participants is asking to be called back. Alternatively, they will be informed to send “Please call me” and the study coordinator will call them back.

Every effort will be made to avoid violence. During the training session, participants will be instructed about assessing client behavior and if a participant is concerned that a client will be violent, she will be counseled not to introduce self-testing with that partner. However, violence from partners may occur and there are measures in place to deal with such cases. For example in cases of rape or non-consensual sex, post-exposure prophylaxis can be administered and trauma counseling done at Impact-RDO Drop In Center (DICE) in Kisumu (TumainiNaselica DICE). Participants who experience violence will be referred to Violence Protection Centre at JOOTRH (JaramogiOgingaOdinga Teaching and Referral Hospital, Kisumu) for medical care (if necessary) and psychosocial services. Other options include reporting to the police for possible legal action. All these options will depend on the complainant. All of this information will be shared with participants during the counseling session and also available via the hotline number.

# ETHICAL CONSIDERATIONS

## Informed Consent

Before studyenrollment, womenwill be introduced to the study and its aims, as outlined in the informed consent document. The consent forms will describe the study procedure in the language (English, Swahili or Dholuo) preferred by the participant. The subject will be asked to read and review the document. Interviewers will be careful to impress upon subjects that they may choose to decline participation or withdraw from the study at any time. Those who agree to participate in the study will be asked to sign and date the informed consent form prior to enrollment and random assignment. If a subject cannot read, the consent form will be read to them and oral consent will be obtained,with a witness providing his or her signature. A copy of the informed consent document will be given to the subjects for their records.

## Ethical Approval

All study participants will be fully informed of the study procedures as described above. Ethical approval for this study will be sought from the Kenya Medical Research Institute’s (KEMRI) Ethical Review Committee and the Institutional Review Board at UNC-CH.

## Protecting privacy and confidentiality

All study staff will undergo ethics trainingand sign a confidentiality agreement (Appendix7: Confidentiality statement). All education, counseling and testing will be done as stipulated in Kenya’sNational Guidelines for HIV testing and counseling. All participants will be identified using a unique identification code that will be assigned to them at the first visit.

All electronic datacollection will take place on encrypted, password-protected tablet computers. Data will be sent to encrypted servers and will only be accessible to authorized study personnel. Consent forms and other paper materials will be stored in locked cabinets with access restricted to authorized study personnel.

## Potential risks of proposed research to study participants

We anticipate minimal risks to study participants. Although there is a potential for exposing a participant’s personal information to others during the interview, every consideration will be taken to ensure the interview is conducted in a private place. Study procedures will be thoroughly explained to participants and they will be consented only if they fully understand study procedures and find them acceptable. Participants are allowed to exit from the study at any time.

We do not anticipate any adverse events following the self-testing, outside normal reactions similar to those occurring among persons testing for HIV the first time.These may include negative reactions to an HIV diagnosis or incorrect test results. Participants will be advised to visit a voluntary counseling and testing (VCT)clinic for a confirmatory test as the self-test is a primarily a screening test. The participants will be well trained on self-testing and counseled before being given the test kits. They will also be given a phone number they can call at any time.The information given will instruct the participants about the potential benefits to using the test prior to sex with a partner (for example, knowing partner’s status before sex can lead to better risk reduction). They will also practice and become comfortable using the kits during this session. All of this will take place at the time of enrollment.

There is a risk that sexual partners will react adversely to the participants’suggestions of self-test usage or to the test result itself. To minimize this risk, we will provide detailed information on the need for confirmatory testing and the availability of HIV care and treatment for HIV-infected persons. We will not enroll women who self-report concern that their partner may hurt them if they suggest using the HIV self-test and in addition we will refer men and women who experience violence forto IPV services.

## Potential benefitsof proposed research to study participants and others

Study participants will havethe opportunity to receiveHIV self-tests to use themselves and to use with their sexual partners. The benefits to participants include increased knowledge about their own HIV status and potentially their partners’ HIV status, which in turn may serve to reduce their risk of HIV infection.

The knowledge gained from this study will also help inform policy makers and HIV prevention programs about the potential role that HIV self-tests can play in increasing awareness of HIV status and reducing the number of new HIV infections.

1. **DATA MANAGEMENT**

## Data storage

All study computers and records will be stored in a secure room with access limited only to authorized staff. All computers and databases will be encrypted and password-protected with limited access. Daily backup of the data will be done by a designated study staff onto a secure server at UNC-CH.

Data collection forms will be stored at IRDO HQ in Kisumu, which will be the operating headquarters of the study. No participants will have any identifier on the data forms; names and signatures will only be on the consent forms, which will be kept under lock and key by the Study Coordinator and after signing, will be accessible only to the PIs, Coordinator and IRDO’s Research Officer. All electronic data collection will take place on encrypted, password-protected tablet computers. Data will be sent to and stored on encrypted, password-protected servers at UNC and will only be accessible to authorized study personnel. At the end of the study, data will be kept for up to 5 years for electronic version and up to 2 years for paper forms, including consent forms. The site PI (KA) will take responsibility of all study procedures, including long-term storage and disposition of data.

## Data management

All statistical analyses will be performed using Stata.

Among the women screened for eligibility, we will first tabulate the reasons for ineligibility.

**Baseline data**

We will use the baseline data to summarize various characteristics of study participants, including age, marital status, education, sexual behavior, and recent HIV testing history. We will report various statistics of the quantitative variables (mean, median, variance, range, IQR, etc.) as well as frequencies for the categorical variables.

**Follow-up data**

We will use the follow-up data to determine the following statistics for each group of participants:

1. Proportion of partners who report that their partner used an HIV self-test
2. Proportion of participants who report that they discussed HIV testing with their partner
3. Proportion of participants whose partners undergo HIV testing individually (partner testing)
4. Proportion of participants who undergo couples HIV testing with their partners
5. Proportion of participants who report mutual disclosure of HIV status with their partner
6. Proportion of participants who reported making sexual behavior decisions (sexual intercourse, condom use) on the basis of a sexual partner’s decision to use or not use the self-test and on the basis of a sexual partner’s test result
7. Proportion of participants who reported that their partner sought confirmatory testing after using the self-test
8. Reports of social harms, such as IPV or coercion as a result of discussing or using HIV self-test

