Novel data are also needed to determine whether the provision of multiple self-tests to women for the purpose of promoting partner or couples testing can be done without increasing the risk of intimate partner violence (IPV).One concern with the promotion of couples HTC in ANC settings has been IPV if one or both partners test HIV-positive. Results to date have been mixed; one randomized controlled trial (RCT) showed no effect of couples HTC on IPV whereas two observational studies found that women who received couples HTC reported more physical violence (3.3%) than women who receiving individual HTC (1.1%)[37-39]. It is important to establish whether IPV is any more likely to occur when women provide their partners with a self-test for individual use or when they initiate couples testing using self-tests. By virtue of being the first attempt to promote partner or couples testing using self-tests, our intervention and accompanying evaluation will provide much-needed evidence to determine whether such testing should be a paradigm that is adopted more widely.

Our intervention builds upon existing work that we have done to explore the acceptability and feasibility of an approach to provide self-tests to index persons for the purpose of promoting more widespread HIV testing in their sexual networks.With support from the Bill and Melinda Gates Foundation’s Grand Challenges Explorations program, our team has begun implementing a pilot intervention to explore the acceptability and willingness among women in Kisumu to use self-tests with their sexual partners. The early findings from our research will be essential for developing counseling protocols that accompany the intervention and developing strategies that facilitate the ability of women to bring up the issue of self-test usage with their partners.

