### Secondary Outcome Measures

The secondary outcomes for the study will further describe uptake of HTC in the intervention and control groups. In particular, we will compare the following outcomes between the two study groups:

Discussions about and uptake of HIV testing:

- Proportion of participants who report that they discussed HIV testing with their partner;
- Proportion of participants whose partners undergo HIV testing individually (partner testing);
- Proportion of participants who undergo couples HIV testing with their partners;

In accordance with WHO guidelines, we define partner testing as a scenario in which one partner (for example, women who participate in our study) has already tested and the other partner (the primary sexual partner of the women) is tested separately without mutual disclosure of HIV status necessarily occurring. On the other hand, couples testing is defined as a scenario in which both partners are counselled, tested, and provided with their results together so that mutual disclosure of HIV status occurs.

Actions taken after HIV testing:

- Sexual behavior and decision making (such as condom use) after HIV-positive and HIV-negative test results for partners;
- Adverse reaction to a positive or discordant result

Since confirmatory testing is recommended following the use of HIV self-tests, in the intervention groupwe will also measure *use of confirmatory testing*by individuals who were reported to have used the self-tests. Participants will be given referral vouchers for confirmatory testing at several VCT clinics in Kisumu so that this can be recorded. We will also obtain self-reported information from the study participants about whether each person who used the self-test sought confirmatory testing.

We will also describe several aspects of self-test usage (where it takes place, how often women suggest the self-test usage to their partners, what reactions male partners have to self-test, etc.).During the follow-up interview we will ask to see the used self-testing package if study participants report that they or their male partner used the self-test.

We will also report outcomes related to social harms, such as experiences of IPVand increase in unprotected sex, if they occur.

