**Follow-up interviews**

Follow-up interviews with participants in the control and intervention groups will be conducted by trained counselors 3 months after enrollment in order to learn about decision-making regarding partner or couples testing. In the control group, we will obtain information from participants on whether they asked their partner to accompany them to the ANC and use the referral voucher for voluntary HTC. In the intervention group, we will obtain information from participants on whether they suggested usage of the self-test to their partner, whether their partner used the self-test, and whether the couple used self-tests together (with mutual disclosure of HIV status) or if instead the partner was believed to have used the self-test alone. In cases where self-tests were reported to have been used, trained HTC counselors will also ask to see the self-tests and obtain visual confirmation of usage. We will also obtain self-reported information on whether partners who used self-tests sought confirmatory testing (those who did not but wish to have their results confirmed during the visit will be tested by the counselor) and whether partners who obtained an HIV-positive test result sought care at an HIV clinic.

In both groups, we will ask participants whether their partners have accompanied them for ANC or PPC visits in the past 3 months. We will also ask participants if their partners have sought care at an HIV clinic in case an HIV-positive test result was obtained. Finally, in both groups, we will inquire about adverse eventssuch as reports of verbal abuse or physical violenceduring the follow-up interview; those who report events will be referred for support. The study will provide a 24-hour hotline that participants can call with questions or to report an adverse event. The hotline will be staffed by trained study personnel who will be available to counsel and provide referrals to participants. If any adverse events are reported, they will immediately be reported to the Ethical Review Boards and action will be taken where possible.

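### Two secondary outcomes listed for between-arm comparison exist only where the partner tested, and the listed social-harm statistic is defined by a self-test that control women are not given

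*Protocol*

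**What the plan says.** **Secondary Outcome Measures** introduces a set of outcomes to be compared between the two study groups. Under actions taken after testing it lists "Sexual behavior and decision making (such as condom use) after HIV-positive and HIV-negative test results for partners" and "Adverse reaction to a positive or discordant result". The same section ends with an undertaking to report social harms, including IPV and more unprotected sex, with no link to the self-test.

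**Statistical analysis** plans logistic regression for the effect of the intervention on the secondary outcomes already defined, and names incidence of adverse events among them.

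**Follow-up data** (under Data management) says the team will "determine the following statistics for each group of participants". Item 8 of that list is "Reports of social harms, such as IPV or coercion as a result of discussing or using HIV self-test". Item 6 counts women who made sexual-behaviour decisions "on the basis of a sexual partner’s decision to use or not use the self-test" and "on the basis of a sexual partner’s test result".

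**Follow-up interviews** says that "in both groups, we will inquire about adverse eventssuch as reports of verbal abuse or physical violenceduring the follow-up interview". This question carries no self-test condition.

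**Control Group** provides standard care and referral coupons redeemable at a VCT centre. No study self-test is given. **Limitations** adds that women in both arms will be asked about partner testing by any route, self-testing included.

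**The concern.** There are two separate problems.

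The first is conditioning on an event after randomisation. Behaviour after a partner's result, and a reaction to a positive or discordant result, can be observed only where the partner tested. Partner testing is the primary outcome, and the trial hopes to move it. The women who contribute in each arm are therefore selected by the intervention. A difference between them mixes any effect on behaviour with a difference in which couples came to be tested.

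The second is a harm definition that applies to one arm only. Item 8, and the first half of item 6, depend on a self-test that control women are not given. Violence after a voucher referral would not count under item 8, while violence after a self-test would. The Justification section wants to learn whether giving out self-tests raises the risk of partner violence. That needs the same definition in both arms. The protocol holds an attributed and an unattributed version, and does not say which one feeds the regression of adverse events.

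**Working it through.** **Inputs.** From Sample size justification: 300 women per arm, 20% partner testing in control, 30% in the intervention arm, 80% power. From Statistical analysis: two-sided 0.05. The protocol gives no figure for the harm or behaviour outcomes.

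**The plan's own figure.** Two proportions, pooled variance, no design effect:

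z = (0.10·√300 − 1.96·√(2·0.25·0.75)) / √(0.20·0.80 + 0.30·0.70) = (1.732 − 1.200) / 0.608 = 0.874, so power is 0.809.

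This agrees with the stated 80%. It does not test the present point; it only confirms the planning rates used next.

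**Size of the result-conditioned groups.**
- Control: 300 × 0.20 = 60 women with a tested partner.
- Intervention: 300 × 0.30 = 90.

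The groups restricted to a positive or discordant result are smaller still.

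**How selection alone can make a difference.** Assume that the 20% who would test under control would also test under the intervention, and that 60% of those couples use condoms afterwards. Assume that the further 10% who test only because of the intervention do so at 30%. The intervention changes nobody's condom use.
- Control, among tested: 60%.
- Intervention, among tested: (0.20 × 0.60 + 0.10 × 0.30) / 0.30 = 50%.

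The ten-point gap is entirely selection. The 60% and 30% are assumed; the direction would reverse if they were swapped.

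**Taking all women as the denominator instead.** If the chance of a positive or discordant result and of an adverse reaction to it were the same in both arms, the proportions would stand in the ratio 0.30 / 0.20 = 1.5. That reflects testing uptake, not a riskier way of testing.

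**Item 8 if it were compared between arms.** With x attributed reports in 300 intervention women and none in 300 controls, two-sided Fisher p = 2 × C(300, x) / C(600, x).

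| x vs 0 | p |
|---|---|
| 5 | 0.061 |
| 6 | 0.030 |
| 8 | 0.007 |
| 9 | 0.0037 |

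The value of x when true IPV is equal in both arms depends on two assumed quantities, the background rate and the share attributed to the self-test:
- 3.3% background, 50% attributed: 300 × 0.033 × 0.50 ≈ 5 (p = 0.061).
- 10% background, 25% attributed: 300 × 0.10 × 0.25 = 7.5, about 8 (p = 0.007).
- 3% background, all attributed: 300 × 0.03 = 9 (p = 0.0037). This is the worst case.

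**The harm wordings side by side.** Follow-up data item 8 is attributed to the self-test. Follow-up interviews, the closing lines of Secondary Outcome Measures, and incidence of adverse events in Statistical analysis are not. These do not describe one outcome.

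**The case against.** The best defence concerns harm. Verbal abuse and physical violence are asked about in both arms without attribution, Secondary Outcome Measures reports IPV in general, and Statistical analysis models adverse events in the same terms as the interview. The Follow-up data list names no test, and it is loosely worded elsewhere: item 7 covers confirmatory testing after the self-test, which Secondary Outcome Measures confines to the intervention group. Item 8 may be no more than a slip. Most of this stands. It leaves a conflict of definitions to settle, not a missing safety comparison.

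A reader might go further in three ways that the protocol does not support:
- *That social-harm outcomes in general are zero by construction in control.* Only item 8 and the first half of item 6 depend on the self-test. Even there, near zero is the accurate term, since Limitations allows for self-testing reported in either arm.
- *That violence in control women would be missed.* They are asked about it at follow-up, and the study hotline is open to participants.
- *That low power for IPV is an error.* At the 1.1% and 3.3% cited in Justification, power with 300 per arm is about 45%. But those rates compare individual with couples testing in other studies, the trial is sized on its primary outcome, and the protocol never says that a non-significant result would be read as safety.

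None of this answers the result-conditioned outcomes. They are expressly listed for comparison between groups, and regression is planned on the secondary outcomes.

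**Conclusion.** The point holds in limited form and touches secondary outcomes only; the primary outcome is unaffected.

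The two post-result outcomes cannot support a randomised comparison as written. At the planned rates they rest on about 60 and 90 women selected by the event that the intervention is designed to change. How large the bias would be is unknown, and the ten-point example rests on assumed condom-use rates.

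Item 8 and the first half of item 6 cannot be compared fairly between arms, and item 8 conflicts with the unattributed harm wording elsewhere. The threshold of six reports against none (p = 0.03) follows from the sample size and a zero control count. Whether six would occur without a true difference depends on the assumed background rate and attribution. The 9 against 0 example is a worst case under full attribution, and it matters only if item 8 is tested between arms, which the protocol does not state.

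**What to change.** - Reword item 8 of Follow-up data as any IPV or coercion since enrolment, whatever the cause, asked identically of all randomised women. State in Statistical analysis that this is the harm outcome for the between-arm comparison.
- Compare sexual behaviour between arms in all randomised women, for example condom use since enrolment, whether or not the partner tested.
- Keep self-test-attributed harms, decisions tied to the partner's use of the self-test, and post-result behaviour or reactions as within-arm description. Take the post-result items out of the list for between-group comparison.

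The cost is mostly wording, with two caveats. All-cause IPV includes events unrelated to testing, so the contrast is less specific. The sponsor must also check that the follow-up questionnaire (Appendix 5, not reproduced in the protocol text) asks about coercion or sexual IPV and about condom use in both arms. Follow-up interviews names only verbal abuse and physical violence, as examples, so an item may have to be added.
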